## Abstract

**Background:**

Successful return to work is regarded as one of the most important outcome factors for working-age post stroke patients. The present study will estimate the effect of various predictors on the odds of returning to work after stroke. Nearly twenty thousand 20-57 year-old stroke patients in Denmark who were gainfully occupied prior to the stroke will be included in the study.

**Methods/design:**

Stroke patients will be followed prospectively through national registers. Multi-level logistic regression will be used to model the odds of being gainfully occupied ca. two years after the stroke as a function of the following predictors: Age (20-49 years, 50-57 years) gender, occupational class, self-employment (yes; no), onset calendar year (1996, 1997, ..., 2006), diagnosis (subarachnoid haemorrhage; intracerebral haemorrhage; cerebral infarction; stroke, not specified as haemorrhage or infarction) and 'type of municipality' (the variable is set to 1 if the person lived in a municipality which had a brain injury rehabilitation centre at the time of the stroke. Otherwise it is set to 0).

Municipalities will be treated as the subjects while individual observations within municipalities are treated as correlated repeated measurements.

**Discussion:**

Since our follow-up is done through registers and all people in the target population are included, the study is free from sampling bias, recall bias and non-response bias. The study is also strengthened by its size. The major weakness of the study is that it does not contain any stroke severity measures. Thus, it cannot accurately predict whether a particular stroke patient will in fact return to work. The study is, however, quite useful from a public health perspective. It can be used to estimate the proportion of patients in a certain group that is expected to return to work, and thereby provide a comparison material, which e.g. municipalities can use to evaluate their success in returning their stroke patients to work.

## Background

Successful return to work (RTW) after stroke can enhance both recovery and life satisfaction by consolidating self-esteem, confidence and social identity [1], and it is regarded as one of the most important outcome factors for working-age post stroke patients [2,3].

RTW is of significant importance not only from the human but also from the societal perspective. The consequences of stroke are extremely costly. In 2008, the annual direct cost of stroke in the 27 EU countries was estimated at €18.5 billion, while the indirect cost in terms of lost productivity due to disability or death was estimated at €8.5 billion [4]. In the United States, loss of earnings is expected to be the highest cost contributor in the time period 2005 to 2050 [5].

Recently, Daniel et al. [6] reviewed 70 studies, which reported post-stroke employment status. In total, the 70 studies included 8810 patients working before the stroke. According to Daniel et al., only three of the 70 studies [7-9] used appropriate analytic strategies. "In all other studies, either time of follow-up was highly variable or interpretation of results was compromised by problems with definition of work before stroke and at follow-up or results were likely to be confounded by selection bias" [6]. The three appropriately performed studies were, however, quite small (the sample sizes ranged from 109 to 173) and two of them [7,8] used data from the 1980's, which are too old to afford results that can be used as proxies for present time RTW probabilities. In the most recent of the three studies [9], 55% of previously employed stroke patients returned to paid employment within six months. That study included, however only cognitively competent patients and is therefore selection-biased.

The present study will investigate return to work frequencies among nearly twenty thousand 20 - 57 year-old stroke patients in Denmark who were gainfully occupied prior to the stroke. The study covers stroke that occurred in the time period 1996 - 2006.

## Methods/design

The study will use the Danish Occupational Hospitalisation Register (OHR), a database obtained through a record-linkage between three national registers--the central person register, the hospital register, and the employment classification module. Currently, the OHR includes every person who has been economically active and an inhabitant of Denmark sometime after 1980.

The national hospital register has existed since 1977 and contains data from all public hospitals in Denmark (more than 99% of all admissions). From 1977 to 1994, the register only included inpatients but from 1995 it also covers outpatients and emergency ward visits [10]. The diagnoses have been coded according to international classification of diseases version ten (ICD-10) since 1994.

The central person register contains information on gender, addresses and dates of birth, death and migrations for every person who is or has been an inhabitant of Denmark sometime between 1968 and present time. A person's occupation and social status are, since 1975, registered annually in the employment classification module [10]. The occupations are, since 1994, coded in accordance with Statistics Denmark's Standard Classification of Occupations (DISCO-88) [11], which is a national version of the International Standard Classification of Occupations (ISCO-88). Socio-economic status is coded in accordance with Statistics Denmark's official socio-economic classification [12]. At the one- and two-digit level, the classification contains the following social groups:

1. Gainfully occupied people

1.1. Self-employed people

1.2. Assisting spouses

1.3. Employees

2. People on unemployment benefits

3. Not economically active

3.1. People in training/education

3.2. Pensioners

3.3. Other not economically active

### Inclusion criteria

A person will be included in the study if he/she

1. on at least one occasion in the time period 1996 - 2006, was registered in the hospital patient registry with one of the following ICD-10 codes as principal diagnosis:

• I60 subarachnoid haemorrhage

• I61 intracerebral haemorrhage

• I63 cerebral infarction

• I64 stroke, not specified as haemorrhage or infarction

2. belonged to the age interval 20 - 57 years at the time of the hospital contact

3. was gainfully occupied the year preceding the hospital contact

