### Statistical analysis

The study will consist of two parts, one is descriptive while the other utilises statistical inference techniques to test hypotheses and estimate odds ratios for RTW (return to work).

In the descriptive part we follow the stroke patients for five calendar years after the stroke and register their main social status in each of these years. This part of the study will only include people who were less than 55 years at the time of the stroke. For any given patient, the calendar year of the stroke will be defined as year 0, the next calendar year will be defined as year 1 etc.

In the regression analysis, we will look at the odds of having a socio-economic code, which indicates gainful occupation in year 2 after stroke. The outcome variable is set to 1 if the person is self-employed, assisting spouse or employee in that particular year. It is set to 0 if the person is unemployed, not economically active or dead.

As explanatory variables we will use gender, age, diagnosis, calendar year, occupational class, self-employment, and type of municipality.

Age at the time of the stroke will be divided into the categories 20 - 49 years and 50 - 57 years. In Denmark it is possible to retire at the age of 60, regardless of health condition. This is why we do not include people who would be older than 60 years at follow-up. The cut-point 50 years conforms to OECD's definition of older workers [13], who are known to have a more insecure labour market attachment than the younger ones.

The variable 'Diagnosis' contains the four stroke categories given in the section 'inclusion criteria'.

The variable 'Self-employment' is set to 1 if the person is self-employed or assisting spouse and 0 if he/she is an employee, the year preceding the stroke.

The variable 'Occupational class' is based on the first digit of the DISCO-88 classification the year preceding the stroke. It contains the following categories:

• Legislators, senior officials and managers (DISCO-88 group 1)

• professionals (DISCO-88 group 2)

• technicians and associate professionals (DISCO-88 group 3)

• workers in occupations that require skills at a basic level (DISCO-88 group 4 - 8)

• workers in elementary occupations (DISCO-88 group 9)

• gainfully occupied people with an unknown occupation (missing DISCO-88 code)

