It is also reasonable to believe that RTW probabilities depend on place of residence. In Denmark, municipalities play an important role in the return to work process. According to the law, it is the municipal officer and not the physician who has the formal right to decide whether or not a person qualifies for sickness benefit, disability pension, or vocational rehabilitation. The law also stipulates that the municipality should perform regular follow-up evaluations and draw up detailed reintegration plans for each sick-listed citizen at risk of long-tem sickness absence [17]. RTW initiatives are often launched at the municipality level and some municipalities might be more active than others. The unemployment situations may also differ between municipalities. In the present study, we will use a multi-level analysis to deal with intra-municipality correlations -- the municipalities are treated as the subjects while the individual observations within the municipalities are treated as correlated repeated measurements.

The logistic regression will be performed by use of the GENMOD procedure in SAS version 9.1. Only main effects are considered. An exchangeable correlation structure is assumed. The empiric standard error estimates will be used.

Table 1 shows how the results from the first part of the study will be presented. Table 2 will list odds ratios and P-values that will be estimated in the second part of the study. Odds ratio for return to gainful occupation two year after stroke, by onset calendar year, will be illustrated by a graph. The calendar year 1996 will be used as reference. All hypotheses are two-tailed. A P-value will be deemed statistically significant if it is less than 0.05.

**Table 1 T1:** Social group distribution (%) by time passed since onset of illness, among stroke patients in Denmark who were 20-54 year of age and gainfully occupied at the time of the stroke

Social status	Year after stroke				
	1	2	3	4	5
Self-employed people					
Assisting spouses					
Employees					
People on unemployment benefits					
People in training/education					
Pensioners					
Other not economically active					
Deceased					

Total	100	100	100	100	100

**Table 2 T2:** Odds ratios (OR), with 95% confidence interval (CI) for return to gainful occupation two year after stroke

Parameter	Level	N	OR	95% CI
Gender (P = xxx)	Men		1.00	-
	Women			
Age (P = xxx)	<50 years		1.00	-
	50 - 57 years			
Diagnosis (P = xxx)	Subarachnoid haemorrhage			

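### Any stroke-coded contact in 1996-2006 is treated as stroke onset, with no exclusion of earlier strokes and no index rule, so old cases can be dated as new and the return-to-work and calendar-year results biased

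*Protocol article*

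**What the plan says.** The Inclusion criteria section is a numbered list of three conditions. A person qualifies who "on at least one occasion in the time period 1996 - 2006, was registered in the hospital patient registry" with I60, I61, I63 or I64 as principal diagnosis, was aged 20-57 at the contact, and "was gainfully occupied the year preceding the hospital contact". The list does not require a first stroke, set a washout, restrict the type of contact or choose among several contacts.

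On contact types, Methods/design says that up to 1994 "the register only included inpatients but from 1995 it also covers outpatients and emergency ward visits". On the history available, it says "The national hospital register has existed since 1977 and contains data from all public hospitals in Denmark", with diagnoses "coded according to international classification of diseases version ten (ICD-10) since 1994".

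The analysis is dated from the stroke rather than the contact. In Statistical analysis, "the calendar year of the stroke will be defined as year 0", and the regression outcome is gainful occupation in year 2. The Abstract names the calendar-year predictor by onset, and the title of Table 1 counts time from onset of illness. Calendar year enters as a class variable, its odds ratios are to be graphed, and "The calendar year 1996 will be used as reference". The Discussion says the study is free of sampling bias and lists limitations, but prior stroke is not among them.

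**The concern.** Eligibility hangs on a hospital contact, while the analysis hangs on a stroke. For a first stroke the two dates coincide. For a person with an older stroke who has a follow-up contact or a recurrence in the window, they do not, and year 2 is then not two years after onset.

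The third criterion adds selection. It looks at work in the year before the contact. A person whose stroke came before that year is admitted only if at work after it, and those who never returned are left out. That comes close to selecting on the study's own outcome.

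The effect need not be even over calendar years. If each person is indexed at the first contact in the window, a person with a stroke in 1997 and a follow-up contact in 2003 is already counted in 1997, whereas nothing removes a person with a stroke in 1990 and a contact in 1996. Unrecognised old cases would then be most common in 1996, the reference year. If some other rule is used, a person can be indexed at a later contact after a successful return.

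Two outputs are at stake: the return-to-work proportions, which the Discussion offers to municipalities as a benchmark, and the calendar-year odds ratios, which the protocol motivates by improving treatment and by policy changes from 1998 to 2005.

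**Working it through.** **1. The plan's own figure.** Inputs from Power calculations: N = 20 000, 10% self-employed, 55% returned, variance × 1.2, odds ratio (OR) 1.3, two-sided alpha 0.05.

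SE(log OR) = √{1.2 × [1/(2000 × 0.55 × 0.45) + 1/(18 000 × 0.55 × 0.45)]} = 0.0519.

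Power = Φ(ln 1.3 / 0.0519 − 1.96) = Φ(3.10) = 99.9%. The stated figure of at least 95% is satisfied and is not in dispute. At N = 18 000 the power is 99.8%, so a moderate loss of patients is affordable.

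**2. Who enters as an old case.** Take a contact in 1996.
- Stroke in 1990-1994: work in 1995 is work after the stroke, so only people at work again enter. Onset is misdated by two to six years.
- Stroke late in 1995: main status for 1995 may reflect work before the stroke. Onset is misdated by one year, but the person is not a proven returner.

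**3. Size of the bias.** The document gives neither the share of old cases nor their work rate, so both are assumed. Let s be the share of old cases in a year and r the proportion of them working in year 2. Incident cases return at the plan's 55% in every year, so the true OR is 1.

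p(year) = (1 − s) × 0.55 + s × r; OR = odds(2006) / odds(1996).

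Patients per year: 20 000 / 11 ≈ 1818. The SE of a year contrast is about √{1.2 × 2/(1818 × 0.2475)} = 0.073.

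Example (10% in 1996, 0% in 2006, r = 80%): p(1996) = 0.9 × 0.55 + 0.1 × 0.80 = 0.575; OR = (0.55/0.45)/(0.575/0.425) = 1.222/1.353 = 0.90.

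| Old cases 1996 / 2006 | r | Return 1996 | Return 2006 | OR 2006 vs 1996 | Chance of P < 0.05 |
|---|---|---|---|---|---|
| 5% / 2% | 70% | 55.75% | 55.3% | 0.98 | 6% |
| 5% / 0% | 70% | 55.75% | 55.0% | 0.97 | 7% |
| 5% / 0% | 80% | 56.25% | 55.0% | 0.95 | 11% |
| 10% / 3% | 70% | 56.5% | 55.45% | 0.96 | 9% |
| 10% / 3% | 80% | 57.5% | 55.75% | 0.93 | 16% |
| 10% / 0% | 80% | 57.5% | 55.0% | 0.90 | 28% |
| 10% / 0% | 55% | 55.0% | 55.0% | 1.00 | 5% |
| 10% / 0% | 40% | 53.5% | 55.0% | 1.06 | 13% |

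The sign depends on whether old cases work more or less often than incident cases. In this table the 1996 proportion moves by −1.5 to +2.5 percentage points.

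**4. Look-back available.** For a 1996 contact, inpatient records go back about 1996 − 1977 = 19 years, ICD-10 codes about 2 years, and outpatient and emergency records about 1 year. For a 2006 contact the same sources give about 29, 12 and 11 years. A look-back to a fixed date is therefore about ten years shorter for 1996 than for 2006 and would leave a calendar gradient of its own.

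**The case against.** The stated target is stroke patients who were working before the stroke; it is never limited to first strokes. A genuine recurrence in a working person fits that target and the municipal use, and excluding it narrows the question. This stands as far as recurrences go. It does not cover a follow-up contact dated as a new stroke, and the criteria give no means of telling the two apart.

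A reader might infer that the old cases had all returned to work, so that return-to-work figures are certainly raised and the 1996 reference certainly inflated. The document does not support this. Recurrent cases may work less often than 55%, which reverses the sign. People with a stroke late in the preceding year can qualify on work done before it. The concentration in 1996 requires the first in-window contact to be the index, which is not stated.

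A reader might also press the size further: 20% old cases in 1996, 80% of them working and none in 2006 would give p(1996) = 0.60 and an OR of (0.55/0.45)/(0.60/0.40) = 0.81. That needs three unsupported extremes at once. In particular, a person with a stroke before 1996 can still have a first in-window contact in 2006, so zero in that year is a worst case.

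Finally, an article condenses its protocol. Here, however, the criteria are given as a list and, followed as written, admit these cases. It is also fair to say that calendar year is only one of seven explanatory variables and that no material bias in the other six has been shown.

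**Conclusion.** The concern holds in this form: eligibility by any qualifying contact, with no exclusion of earlier strokes and no index rule, lets old cases be dated as new onsets. Most of those whose stroke predates the year before the contact enter only if at work after it. Time since onset is wrong for these patients whatever their number. The return-to-work proportions can be biased, and so can the calendar-year odds ratios if the first in-window contact is the index.

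Size and sign rest on assumptions. For the combinations of 5% against 0-2% and 10% against 0-3% old cases, with 70-80% working, a true OR of 1 becomes about 0.98 to 0.90. That is about 0.2 to 1.4 standard errors of a single year contrast. With 40% working and 10% against 0% it becomes about 1.06. A small effect is possible. This should be fixed, but the document does not show that the calendar-year results would be invalid.

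**What to change.** - Define the index as the person's first contact with principal diagnosis I60, I61, I63 or I64 (I62 is not on the protocol's list), and count each person once.
- Exclude persons with an earlier stroke contact, using a look-back of the same length and the same contact type for every calendar year. Inpatient records with the corresponding pre-1994 codes allow up to about 19 years. At least ten years (2006 − 1996) is advisable: with a shorter look-back, the count-once rule would still screen later years more thoroughly than 1996.
- State which contact types can serve as the index, and repeat the analysis with the index restricted to inpatient admissions.
- Report how many persons the look-back removes in each calendar year, which replaces the assumed shares above with data.

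The cost is one added criterion and a query in a register that is already linked, plus a mapping of the older codes. The sample falls somewhat below 20 000, and the results apply to first strokes within the look-back. Power is not a constraint: even 18 000 patients give 99.8% for the plan's own contrast.

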### Statistical analysis

The study will consist of two parts, one is descriptive while the other utilises statistical inference techniques to test hypotheses and estimate odds ratios for RTW (return to work).

In the descriptive part we follow the stroke patients for five calendar years after the stroke and register their main social status in each of these years. This part of the study will only include people who were less than 55 years at the time of the stroke. For any given patient, the calendar year of the stroke will be defined as year 0, the next calendar year will be defined as year 1 etc.

In the regression analysis, we will look at the odds of having a socio-economic code, which indicates gainful occupation in year 2 after stroke. The outcome variable is set to 1 if the person is self-employed, assisting spouse or employee in that particular year. It is set to 0 if the person is unemployed, not economically active or dead.

As explanatory variables we will use gender, age, diagnosis, calendar year, occupational class, self-employment, and type of municipality.

Age at the time of the stroke will be divided into the categories 20 - 49 years and 50 - 57 years. In Denmark it is possible to retire at the age of 60, regardless of health condition. This is why we do not include people who would be older than 60 years at follow-up. The cut-point 50 years conforms to OECD's definition of older workers [13], who are known to have a more insecure labour market attachment than the younger ones.

The variable 'Diagnosis' contains the four stroke categories given in the section 'inclusion criteria'.

The variable 'Self-employment' is set to 1 if the person is self-employed or assisting spouse and 0 if he/she is an employee, the year preceding the stroke.

The variable 'Occupational class' is based on the first digit of the DISCO-88 classification the year preceding the stroke. It contains the following categories:

• Legislators, senior officials and managers (DISCO-88 group 1)

• professionals (DISCO-88 group 2)

• technicians and associate professionals (DISCO-88 group 3)

• workers in occupations that require skills at a basic level (DISCO-88 group 4 - 8)

• workers in elementary occupations (DISCO-88 group 9)

• gainfully occupied people with an unknown occupation (missing DISCO-88 code)

The variable 'Type of municipality' is set to 1 if the person lived in a municipality which had a brain injury rehabilitation centre at the time of the stroke. Otherwise it is set to 0. The following municipalities had a brain injury rehabilitation centre throughout the study period: Copenhagen, Odense, Aarhus, Roskilde, Aalborg and Vejle.

There are at least two reasons for believing that the RTW probabilities depended on which calendar year the stroke occurred. Firstly, quality of stroke treatment and rehabilitation has a tendency to improve with time. This is illustrated by two Finish studies which show that 28-day case fatality rates among 35 - 74 year-old stroke patients decreased by approximately three percent annually in the time period 1983 - 2001 [14,15]. A similar trend was observed in England [16]. Secondly, a series of political initiatives and legislative changes, aimed at improving return to work rates in Denmark, occurred during the study period. In 1998, the flexi-job system was introduced, which allows people with permanently reduced work capacity to work part time, yet through public subsidy get full salary. In 2001, the flexi-job system was reformed. A person who is eligible to a flexi-job would be entitled to unemployment benefits if no such work could be found. In 2003, a new disability retirement scheme was introduced. The main intent of the reform was to ascertain that as many as possible retain their attachment to the labour market. A new procedure for assessing work capacity was introduced, and disability pension would only be granted if work ability was permanently reduced and flexi-job work was unfeasible. In 2005, the municipal control of the sick-listed was intensified by a change in the Sickness Benefit Act. Follow-up evaluations were required once a month instead of once every second month, and a reintegration plan was to be drawn up after four instead of six months [17]. To deal with this possible time dependency, we incorporate calendar year into the model as a class variable.

It is also reasonable to believe that RTW probabilities depend on place of residence. In Denmark, municipalities play an important role in the return to work process. According to the law, it is the municipal officer and not the physician who has the formal right to decide whether or not a person qualifies for sickness benefit, disability pension, or vocational rehabilitation. The law also stipulates that the municipality should perform regular follow-up evaluations and draw up detailed reintegration plans for each sick-listed citizen at risk of long-tem sickness absence [17]. RTW initiatives are often launched at the municipality level and some municipalities might be more active than others. The unemployment situations may also differ between municipalities. In the present study, we will use a multi-level analysis to deal with intra-municipality correlations -- the municipalities are treated as the subjects while the individual observations within the municipalities are treated as correlated repeated measurements.

The logistic regression will be performed by use of the GENMOD procedure in SAS version 9.1. Only main effects are considered. An exchangeable correlation structure is assumed. The empiric standard error estimates will be used.

Table 1 shows how the results from the first part of the study will be presented. Table 2 will list odds ratios and P-values that will be estimated in the second part of the study. Odds ratio for return to gainful occupation two year after stroke, by onset calendar year, will be illustrated by a graph. The calendar year 1996 will be used as reference. All hypotheses are two-tailed. A P-value will be deemed statistically significant if it is less than 0.05.

**Table 1 T1:** Social group distribution (%) by time passed since onset of illness, among stroke patients in Denmark who were 20-54 year of age and gainfully occupied at the time of the stroke

Social status	Year after stroke				
	1	2	3	4	5
Self-employed people					
Assisting spouses					
Employees					
People on unemployment benefits					
People in training/education					
Pensioners					
Other not economically active					
Deceased					

Total	100	100	100	100	100

**Table 2 T2:** Odds ratios (OR), with 95% confidence interval (CI) for return to gainful occupation two year after stroke

Parameter	Level	N	OR	95% CI
Gender (P = xxx)	Men		1.00	-
	Women			
Age (P = xxx)	<50 years		1.00	-
	50 - 57 years			
Diagnosis (P = xxx)	Subarachnoid haemorrhage			
	Intracerebral haemorrhage			
	Cerebral infarction		1.00	-
	Stroke, not specified as haemorrhage or infarction			
Self-employment (P = xxx)	No		1.00	-
	Yes			
Occupational class (P = xxx)	Legislators, senior officials and managers			
	Professionals			
	Technicians and associate professionals			
	Workers in occupations that require skills at a basic level			
	Workers in elementary occupations		1.00	-
	Gainfully occupied people NOS			
Municipality type (P = xxx)	Municipality without brain injury centre		1.00	-
	Municipality with brain injury centre			

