### Power calculations

We include all stroke patients of the concerned population and time period. The sample size is therefore fixed at ca. 20 000 persons. The statistical power of the study depends on which factor we consider and what effect sizes we wish to detect. The factor associated with the least power would be self-employment (only ten percent of the concerned stroke patients are self-employed). If we assume that 55% of the stroke patients have returned to stable employment two years after stroke and that intra-municipality correlations inflate the variance with 20% then (based on the central limit theorem and the propagation of error formulas) we have at least a 95% chance of detecting an effect of self-employment if the true odds-ratio between the self-employed and other employees is either greater than 1.3 or less than 1/1.3.

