## Discussion

Our follow-up is done prospectively through registers and does not require that the participants should fill in a questionnaire. Hence we do not have any problems with recall bias or non-response bias. Since informed consent from the participants is not required for register studies of the present type, the study is free from volunteer bias. It is also free from sampling bias since all people in the target population are included. Another advantage of the study is that referral bias is minimal; the diagnoses under study are of a kind that requires hospital treatment. The study is further strengthened by its size.

A drawback of the Occupational Hospitalisation Register is that the occupational and socio-economic data are given per calendar year rather than on a daily basis. We know the person's main occupation and social group during a calendar year but we cannot know the exact date when he returns to work. Due to this shortcoming, a person who returns to work in a given calendar year would still be treated as a non-returner in the analysis if he, for example, was unemployed during the major part of that year. The participants are in other words required to return to stable gainful employment before they are categorised as having returned to work. This can, however, also be regarded as a strength; it has been shown that many people with brain injury who return to work are unable to continue their employment [1].

Overall stroke severity is the most consistent predictive factor for RTW [18]. The major weakness of the present study is that it does not include any such measure. Data on post-stroke neurological impairments such as the presence and degree of apraxia, aphasia and agnosia, would definitely improve our chances of correctly guessing whether or not an individual patient would return to work. Our study is, however, quite useful from a public health perspective. It can be used to estimate the proportion of patients in a certain group that is expected to return to work and thereby provide a comparison material, which e.g. municipalities can use to gauge their success in returning their stroke patients to work.

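### Age is adjusted for only as 20-49 versus 50-57 although dates of birth are linked, which may leave residual age confounding, chiefly in the diagnosis odds ratios

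*Protocol article*

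**What the plan says.** The Statistical analysis section fixes the coding: "Age at the time of the stroke will be divided into the categories 20 - 49 years and 50 - 57 years". Table 2 repeats it, with under 50 as the reference. The same section puts age into one model with all other predictors: "As explanatory variables we will use gender, age, diagnosis, calendar year, occupational class, self-employment, and type of municipality". It adds: "Only main effects are considered".

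The reason given for the cut at 50 is that it matches the OECD definition of older workers, "who are known to have a more insecure labour market attachment than the younger ones". The upper limit of 57 is explained by the possibility of retiring at 60.

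Exact age is available. Under Methods/design: "The central person register contains information on gender, addresses and dates of birth, death and migrations".

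On the use of the results, the Discussion says: "It can be used to estimate the proportion of patients in a certain group that is expected to return to work". Municipalities are to use these proportions to judge their own performance. The limitations discussed are the missing severity measure, the annual resolution of the employment data and the interpretation of municipality type. Age coding is not among them.

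**The concern.** Age does two jobs here. It is a predictor with its own row in Table 2, and it is the adjustment term behind every other odds ratio. The older-worker definition is a sound reason to display a contrast at 50. It is not a reason to treat the 30 years from 20 to 49 as one level when adjusting diagnosis, self-employment or occupational class.

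The protocol itself expects age to matter for labour-market attachment. Death also counts as not returning to work, which is another route by which age could act. Calendar year, by contrast, enters as a class variable with eleven levels, so that no shape is imposed on it.

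Two things are at stake. First, with about 20 000 patients the standard errors are small, so a bias of several percent in an odds ratio raises the chance of a spurious significant result. Second, patients aged 22 and 49 who share all other covariates receive the same fitted RTW probability, which limits how well expected proportions can reflect a municipality's age mix.

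**Working it through.** **The plan's own figure.** Inputs from Power calculations: about 20 000 patients, 10% self-employed (2 000 versus 18 000), 55% RTW, variance inflated by 20%, odds ratio 1.3; two-sided 0.05 from Statistical analysis.

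SE of the log odds ratio = √[1.2 / (0.55 × 0.45) × (1/2 000 + 1/18 000)] = 0.052. Then ln 1.3 / 0.052 = 0.262 / 0.052 = 5.05, and power = Φ(5.05 − 1.96) = 99.9%. The stated bound of at least 95% holds. It does not depend on the age coding and is not in dispute.

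**Assumptions that are not in the protocol.** RTW log-odds fall linearly by 0.01 to 0.04 per year of age. Patient numbers rise per year of age by 10% for infarction and 4% for subarachnoid haemorrhage (set A), or by 8% and 5% (set B). Haemorrhage makes up 15% of patients (3 000 versus 17 000). Overall RTW is 55%. All true odds ratios are 1.00.

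**Diagnosis contrast.** With the two-level term, the spurious log odds ratio is approximately the slope × the average within-band age difference. Bands are weighted by n₀n₁/(n₀ + n₁), where n₀ and n₁ are the infarction and haemorrhage counts in the band.

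| | Set A | Set B |
|---|---|---|
| Mean age under 50, infarction vs haemorrhage | 40.82 vs 37.37 (3.45 years) | 39.81 vs 38.03 (1.78 years) |
| Mean age 50-57, infarction vs haemorrhage | 54.00 vs 53.71 (0.29 years) | 53.90 vs 53.76 (0.14 years) |
| Weights, under 50 and 50-57 | 1 560 and 938 | 1 528 and 1 009 |
| Weighted difference | (1 560 × 3.45 + 938 × 0.29) / 2 498 = 2.26 years | (1 528 × 1.78 + 1 009 × 0.14) / 2 537 = 1.13 years |

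Set A, slopes 0.01, 0.02, 0.03, 0.04: exp(0.023), exp(0.045), exp(0.068), exp(0.090) = 1.02, 1.05, 1.07, 1.09.

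Set B, same slopes: exp(0.011), exp(0.023), exp(0.034), exp(0.045) = 1.01, 1.02, 1.03, 1.05.

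Fitting the planned logistic model to expected probabilities gives nearly the same: 1.02 to 1.09 for set A and 1.01 to 1.04 for set B. The two-level term removes only about half of the age confounding. At slope 0 the odds ratio is 1.00.

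**False positives, diagnosis.** SE = √[1.2 / 0.2475 × (1/3 000 + 1/17 000)] = 0.044. An odds ratio of 1.01 gives z = 0.010 / 0.044 = 0.23 and about 6% rejection. An odds ratio of 1.09 gives z = 0.086 / 0.044 ≈ 2.0 and about 50%. The nominal rate is 5%.

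**Self-employment.** Assume its odds rise 2-4% per year of age and patient numbers rise 10% per year. The same fit gives about 0.97 to 0.99. The steepest combination reaches 0.96 if patient numbers rise by 8% instead. With SE 0.052, an odds ratio of 0.99 gives about 5% rejection and 0.97 gives about 9%. The bias on the log scale, 0.009 to 0.030, is 3-12% of ln 1.3.

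**Expected proportions.** At slope 0.02, expected RTW is about 67% at age 22 and 54% at 49; the under-50 average is 58%. At slope 0.04 the figures are 77%, 53% and 62%. For a municipality what counts is the average age within the band. If its under-50 patients were two years younger than the national group (an illustration), its expected RTW would differ by about 2 × 0.02 × 0.24 ≈ 1 to 2 × 0.04 × 0.24 ≈ 2 percentage points.

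**With finer age.** In the same expected data, 5-year bands return odds ratios of 0.997 to 1.004 and 5% false positives. The SE is essentially unchanged (about 0.044 to 0.046 for the diagnosis contrast).

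**The case against.** The cut at 50 is prespecified and has a policy rationale. The cap at 57 already removes the retirement effect that the protocol documents. Bias needs both an RTW gradient inside a band and within-band age differences between predictor groups, and the protocol reports neither. A linear fall in log-odds is an assumption; if RTW dropped mainly near 50, the two-level term would capture most of it. The missing severity measure, which the protocol calls its major weakness, limits any causal reading of the diagnosis odds ratios more than age coding does. All of this stands, and it makes the point conditional and moderate in size.

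A reader might infer that the diagnosis, self-employment and occupational class odds ratios are certain to be confounded by age. The document does not support that. The diagnosis figures rest on assumed gradients, the self-employment shift is small even under them, and no figure can be given for occupational class.

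A reader might also infer that the municipal benchmark fails. It does not. The Abstract and Discussion claim group proportions and disclaim accurate prediction for an individual patient. A rate for patients under 50 is a valid group average, and it misleads only where the local age mix within the band departs from the national one.

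What the objection does not supply is a reason to adjust for age this coarsely when exact age is at hand. The rationale for 50 concerns where to cut, not whether two levels suffice for adjustment.

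**Conclusion.** The point holds in conditional form. The coding, the availability of dates of birth and the main-effects restriction are all stated in the protocol. Whether the odds ratios are biased, and by how much, depends on gradients that it does not give. Under the assumed ranges, a null odds ratio for subarachnoid haemorrhage versus infarction would be estimated as about 1.01 to 1.09, with roughly 6% to 50% false positives at a 15% haemorrhage share. Self-employment would move to about 0.97-0.99, which matters little. With no age gradient inside the bands the bias is zero. The expected RTW proportions are coarsened, not invalid. The power statement is unaffected. This is an avoidable weakness in the adjustment, not an error or a contradiction, and it merits a change because the remedy is nearly free.

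**What to change.** In the main GEE, adjust for age at stroke with a restricted cubic spline (for example 4 knots) or with 5-year bands. Keep under 50 versus 50-57 as a displayed contrast in Table 2, taken either from average predicted RTW in the two groups or from a secondary model with the two-level term, and say which. Where expected RTW proportions are offered for municipal comparison, derive them from the finer age term so that a municipality can match its own age mix.

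Cost: a 4-knot spline uses three age terms instead of one, so two extra parameters. Eight bands (20-24 up to 50-54, then 55-57) use seven, so six extra. Against about 20 000 patients the loss of precision is negligible, and no new data are needed. The one complication is that the age row of Table 2 then comes from a derived contrast or a secondary model and needs a footnote.
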